## Abstract

A novel smartphone‐based patient support tool was developed to increase the adherence to antiplatelet therapy and lifestyle changes in patients after coronary angioplasty for acute coronary syndrome (ACS). The eMocial study (http://clinicaltrials.gov Identifier: NCT02615704) investigates whether an electronic support tool will improve adherence to comedication and lifestyle changes in ACS patients. The primary hypothesis of this trial is that an electronic support tool can increase adherence to comedication (primary endpoint) thereby supporting positive lifestyle changes (secondary endpoints). Patients hospitalized with ACS (ST elevation myocardial infarction [STEMI], non‐ST elevation myocardial infarction [NSTEMI], or unstable angina pectoris) and treated with ticagrelor coadministered with low‐dose acetylsalicylic acid will be randomized 1:1 to an active group receiving the patient support tool via a smartphone‐based application or to a control group without the patient support tool. Patient questionnaires to evaluate lifestyle changes and quality of life will be used at baseline and at the end of the 48‐week observation phase. Patients are asked to fill out questionnaires to determine their adherence, treatment attitudes, health‐care utilization and risk factors on a monthly basis. The study was started in February 2016 and the completion date is scheduled for October 2019. For final analysis 664 patients are expected be available. Preliminary baseline demographics were unstable angina pectoris (13.7%), NSTEMI (49.9%), STEMI (36.4%), male gender (86.3%), and diabetes mellitus (17.6%). Our study could significantly help to understand how inadequate adherence to antiplatelet therapy in ACS patients could be improved with a smartphone‐based application.

## INTRODUCTION

1

In the United States, approximately 1 365 000 patients are hospitalized for acute coronary syndrome (ACS) annually.^1^ Despite optimal medical therapy, patients with recent ACS remain at high risk of recurrent coronary events.^2^ Therefore, long‐term management for patients discharged after ACS includes lifestyle changes (eg, physical activity plans, smoking cessation, and adherence to a healthy diet), the control of risk factors, and pharmacotherapy using antiplatelet therapy of acetylsalicylic acid (ASA), P2Y_12_ receptor inhibitors, beta‐blockers, statins, angiotensin‐converting enzyme inhibitors, or angiotensin receptor blockers.^3^

In clinical trials, therapy adherence tends to be high, whilst adherence in clinical practice is usually lower.^4^ A key strategy to enhance adherence is better communication and face‐to‐face coaching by a health‐care professional,^5^, ^6^ despite the fact that coaching sessions may not be sustainable from a cost perspective. Digital patient support has been proposed as a potential solution that could be effective at a sustainable cost.^7^, ^8^, ^9^

The purpose of the “Me & My Heart” (eMocial) study is to evaluate if patient support via a smartphone‐based app increases patients' adherence to treatment as compared to the current practice of providing information leaflets to the patients within the German health‐care system.

### Rationale for the study design and focus on platelet inhibition

1.1

Current European Society of Cardiology (ESC) guidelines^3^, ^10^ recommend that antiplatelet therapy with low‐dose ASA, coadministered with P2Y_12_ receptor blockers, should be continued up to 12 months in ACS patients. However, real‐life comedication adherence seems to be an issue.^11^ In the PLATO trial,^12^ ticagrelor (90 mg twice daily) significantly reduced the rate of death from vascular causes, myocardial infarction and stroke without an increase in the rate of overall major bleeding. However, an increase in the rate of non‐procedure‐related bleeding as compared with clopidogrel in ACS patients was observed. The primary composite endpoint of cardiovascular death, myocardial infarction (MI), and stroke at 12 months showed a statistically significant benefit for ticagrelor to support the claim of a continuous benefit throughout the PLATO trial period. This suggests that the full benefit of ticagrelor treatment is achieved when it is continued for the full 12 months, or even longer based on the results of the PEGASUS trial. In the latter trial, ticagrelor (90 or 60 mg twice daily) was administered to patients between 1 and 3 years following MI.^13^ To achieve the full benefit of ticagrelor in clinical practice, treatment adherence and persistence should be at least similar as observed in clinical trials. The overall adherence or adherence rate to ticagrelor in the PLATO trial was 82.8%, and the median comedication duration was 277 days (interquartile range 179‐365).^12^ Limited data are available on ticagrelor adherence and discontinuation rates in general medical care. Moreover, reasons for discontinuation and clinical consequences from premature discontinuation have not been adequately studied.^14^ However, a 100% adherence to DAPT has been shown to significantly reduce the risk of death or secondary MI in stented patients^15^ indicating an unmet need to effectively enhance therapy adherence.

### Patient adherence

1.2

Poor adherence to comedication or lifestyle changes are multifactorial and are the result of an interplay of patient‐, physician‐ and health‐care‐related factors.^16^ Among patients taking oral antiplatelet medication, a lack of awareness regarding their necessity is associated with patient‐reported non‐adherence.^9^ A recent systematic review on long‐term treatment of cardiovascular risk factors suggests cognitive education or behavioral counseling in multiple face‐to‐face meetings may improve that patients' adherence.^7^ Nevertheless, these approaches are not considered cost‐effective due to their resource‐intensive nature for patients and providers. Consequently, these practices have not been widely implemented into general health‐care practice.^7^

We sense that there is a need for alternative, cost‐effective methodologies to improve adherence, which can be customized to individual patient's needs and circumstances.^7^, ^17^, ^18^ A proposed strategy is the use of mobile health (mHealth) technology, which uses smartphone‐ or tablet‐based apps to reach diverse patient populations, including low‐income and otherwise difficult‐to‐reach patients.^19^ Significant improvements in treatment adherence using mHealth approaches have been observed in over 50% of randomized clinical trials for chronic diseases.^19^

### Tools to assess therapy adherence

1.3

A broad range of direct and indirect methods is available to study adherence and persistence of a long‐term, oral drug treatment in clinical practice. However, there is currently no single, “gold standard” approach.^20^ Direct methods include laboratory testing of drug concentration or effect, such as inhibition of platelet activity (IPA). Indirect methods include the assessment of medication possession ratio (MPR), percentage of days covered (PDC), and patient‐reported outcome (PRO) instruments. PDC can be derived from the rates of prescription refills in pharmacy claims databases, or from medication event monitoring systems (MEMS) for pill counts via blister packs, bottles or electronic tablet dispensing devices.

Regarding our primary endpoint measure, there are several self‐reported adherence measures. The Morisky scale^21^ (MMAS) has been used for adherence evaluation in many studies and there are two versions of the MMAS, the four item (MMAS‐4) and eight item (MMAS‐8). It is a generic self‐reported scale^21^ which does not measure adherence per se, but rather medication taking behaviors like unintentional non‐adherence. According to today's standards, the MMAS is considered as non‐validated in terms of both content and from psychometric perspectives.^22^, ^23^ In studies measuring internal reliability for MMAS, many studies have shown low reliability and half acceptable reliability.^24^ However, no single method seems to stand out to deserve a “gold standard” designation.^11^ The PRO instrument used in this study was therefore based on a set of questions on adherence and has been designed for the current setting and measures adherence in a way that captures both intentional and unintentional non‐ adherence and was developed to make it specific for Dual Antiplatelet Therapy (DAPT) and to focus on true adherence irrespectively of the reason why patients did not take DAPT. In addition, we added standard questions regarding health‐care utilization and hospitalization which were part of the secondary endpoints.

The two major reasons for why we created our own instrument are 2‐fold. Today there are no existing PRO measures that are validated and measure adherence. Secondly, the goal of the study was to measure actual compliance which needed to be specific for antiplatelet therapy.

To our knowledge, no available instrument meets today's regulatory standards of being “fit for purpose.” Therefore, we developed a PRO instrument called the Brilique Adherence Questionnaire (BAQ). The BAQ (Appendix A1 and B1, Supporting Information) contains 15 questions measuring both intentional and unintentional non‐adherence. The first four questions refer to the number of tablets the patient has taken and the reasons for not taking them. Questions 5 to 11 capture intentional and unintentional non‐adherence using a three‐stage response option (“never/not at all” to “often/yes completely”).

### Investigational app

1.4

A medical, smartphone‐based app, “Me & My Heart”, has been developed to increase treatment adherence (medication and lifestyle changes) by combining reminders about medication intake, information on the importance of treatment, motivation by supportive messages, and visualization of the effect of an individual's lifestyle choices on cardiovascular risk (specifically for patients with ACS who are prescribed drugs such as ticagrelor). The app is CE (Conformité Européene) marked as a class I medical device. The patient enters baseline information and the tool will then allow the patient to enter data on an ongoing basis and provide individualized feedback to the patient. The app will send daily optional reminders for medication intake, as well as motivational and informative messages every couple of days. The relationship between cardiovascular risks and lifestyle choices is graphically displayed in a qualitative way on a continuous basis.

In addition, the “Me & My Heart” app delivers monthly questionnaires to evaluate the trial endpoints. For the control group, the app will deliver only the questionnaires to evaluate endpoints and will not give any of the previously mentioned patient support. To assess if this information has an effect on the patients' lifestyle, we included an in‐house developed instrument, the Lifestyle Changes Questionnaire (LSQ; Appendix B1), which asks patients about diet, exercise and smoking habits. The 36‐item Short‐Form Health Survey was also included to understand the possible impact on health‐related quality of life (QOL).

## METHODS

2

### Study design and population

2.1

This “Me & My Heart” study (eMocial, http://clinicaltrials.gov Identifier: NCT02615704) is a randomized trial according to §23b Medizinproduktegesetz (German Medical Device Law). The primary objective is to evaluate the effect of patient support delivered through a smartphone‐based app on treatment adherence in ACS patients who received ticagrelor as their antiplatelet agent. More precisely, the primary hypothesis of this trial is that an electronic support tool can increase adherence to comedication (primary endpoint) thereby supporting positive lifestyle changes (secondary endpoints).

Treatment adherence will be measured using questions 1 to 4 in the BAQ every 4 weeks, and a scoring system for quantification from 0 to 14 will be employed. For the scoring system, one deduction for every missed ticagrelor tablet per week with a two‐tablet daily dosing, using a 7‐day recall period will be used and extrapolated to a 4‐week period.

Secondary objectives (Table 1) included the assessment whether the patient support delivered via the smartphone‐based app influenced the patient‐reported changes in disease understanding and treatment (assessed by BAQ questions 5‐11). Furthermore, the usefulness of this smartphone‐based app to improve drug adherence was part of the secondary objectives, that is, the time without antiplatelet medication according to BAQ/MEMS. Moreover, the change from baseline to the second visit in key risk factors was also studied. These risk factors included (a) blood pressure, and (b) laboratory parameters for low density lipoprotein (LDL) cholesterol, high density lipoprotein (HDL) cholesterol, glycated hemoglobin A1c (HbA_1c_), (c) body weight, waist circumference, body mass index (BMI), and (d) quality of life measures (assessed by SF‐36v2); lifestyle changes questionnaire (assessed by LSQ‐V1 and ‐V2); and (e) health‐care utilization (assessed by BAQ questions 12‐15). Details of the SF‐36v2 and LSQ‐V1 and ‐V2 scores are available in Table A1.

**Table 1 clc23254-tbl-0001:** Objectives

Primary objective:	Outcome measure:
To evaluate the effect of patient support delivered through an electronic device application on treatment adherence in patients with ACS prescribed ticagrelor in Germany.	Adherence to prescribed treatment according to questions 1‐4 in the BAQ, including a scoring system for quantification from 0‐14 (ie, one deduction for every missed ticagrelor tablet per week with twice‐daily dosing). The BAQ will be delivered via electronic device every 4 wk; the percentage of tablets taken during a 1‐wk recall period will be extrapolated to 4 wk.

Secondary objectives:	Outcome measures:
To evaluate the effect of patient support delivered via an electronic device application on adherence to ticagrelor medication.	Percentage of tablets taken during the 48‐wk observation phase measured by MEMS to record a time stamp for every tablet taken.
To evaluate the effect of patient support delivered via an electronic device application on the change from baseline to Visit 2 in key risk factors.	Blood pressure, laboratory parameters (if available: low‐density lipoprotein cholesterol, high‐density lipoprotein cholesterol, hemoglobin A_1c_, body weight and body mass index.
To evaluate the effect of patient support delivered via an electronic device application on quality of life.	Assessed by SF‐36v2®, at the start and end of the 48‐wk observation phase.
To evaluate the effect of patient support delivered via an electronic device application on patient‐reported lifestyle changes.	Assessed by LSQ‐V1 and ‐V2, at the start and end of the 48‐wk observation phase.
To evaluate the effect of patient support delivered via an electronic device application on patient‐reported disease understanding and treatment awareness.	Assessed by questions 5‐11 of the BAQ, delivered via electronic device every 4 wk.
To evaluate the effect of patient support delivered via an electronic device application on health‐care utilization.	Assessed by questions 12‐15 of the BAQ, delivered via electronic device every 4 wk.

Abbreviation: BAQ, Brilique Adherence Questionnaire; LSQ, Lifestyle Changes Questionnaire; MEMS, Medical Event Monitoring System; SF‐36, 36‐item Short‐Form Health Survey.

Before hospital discharge, patients diagnosed with ACS and treated with ticagrelor will be offered to participate in the study. It is planned that approximately 680 patients who give informed consent will be randomized 1:1 via an electronic case report form (eCRF) to a 2 × 2 factorial design with equal group sizes to receive the smartphone‐based patient support tool (with additional prompt questions for clinical evaluation) or a control smartphone‐based app used for data collection only (with no patient support). The detailed inclusion and exclusion criteria are described in Table 2. Both the active and control groups will be further randomized 1:1 into two subgroups. One subgroup will use MEMS to record when the patient takes their medication, and the other subgroup will not use the MEMS device (Figure 1). This study is being conducted in accordance with the current Declaration of Helsinki and is consistent with the International Conference on Harmonization and Good Clinical Practice guidelines.

**Table 2 clc23254-tbl-0002:** Inclusion and exclusion criteria

Inclusion criteria	Provision of patient‐informed consent prior to randomization. Female or male aged 18 years or older. Patients with ACS, diagnosed with STEMI, NSTEMI, or UA treated with ticagrelor before inclusion in the study and for whom the treating physician intends to continue prescribing twice‐daily ticagrelor coadministered with low‐dose acetylsalicylic acid, within 14 d following the diagnosis of the ACS event. Ability to read, understand, and write German. Patients must have access to a compatible electronic device and be willing to use it on a daily basis.
Exclusion criteria	Involvement in the planning and/or conduct of the study. Participation in another clinical study with an investigational product or medical device during the last 30 d, excluding prospective/retrospective register‐based studies that do not require any extra clinic visits in addition to ordinary healthcare. Patients being treated with oral antiplatelet drugs other than ticagrelor. Patients with contraindication to the use of ticagrelor. Patients with accepted/planned thoracic surgery (e.g. coronary artery bypass graft) or any other elective surgery that cannot be postponed until after study participation. Presence of serious/severe comorbidities in the opinion of the investigator which may limit life expectancy (< 1 y). Women who are currently pregnant or breast‐feeding.

Abbreviations: ACS, acute coronary syndrome; NSTEMI, non‐ST elevation myocardial infarction; STEMI, ST elevation myocardial infarction; UA, unstable angina pectoris.

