### Endpoints

2.2

The primary outcome variable is the percentage of tablets that patients report to have taken during the 48‐week observation phase, measured by the BAQ. The main secondary outcome variables include the percentage of tablets taken during the 48‐week observation phase, using the information from MEMS. Furthermore, the percentage changes from baseline to the second visit to determine key risk factors (including blood pressure and laboratory parameters), in quality of life (SF‐36v2, see Table A1) and in patient‐reported lifestyle changes (LSQ‐V1 and LSQ‐V2, see Table A1) were studied. Understanding of the disease and treatment awareness as assessed by the BAQ questions 5 to 11, health‐care utilization based on BAQ questions 12 to 15 and cardiovascular risk score (GRACE 2.0, see Table A1) complemented the secondary endpoints.^25^

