The advantage of using a smartphone‐based app (Appendix C) to judge therapy adherence in clinical practice is that actual clinic visits are not required. Furthermore, there are no clinical follow‐ups outside the standard of care during the 12‐month period and no follow‐ups if patients do not complete the surveys after initial enrolment in the study. Thus, the patients will only follow standard of care in the real‐life setting and improvements in adherence will be likely to stem from the benefits of using the smartphone‐based patient support tool app. Based on the same rationale, no prescribed treatment drug is provided in this study.

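### Table 1 limits the Visit 2 laboratory outcomes to available values, but sections 2.1 and 2.2 drop that condition and section 2.3 ranks the risk-factor changes as key secondary endpoints

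*Protocol article*

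**What the plan says.** For the objective on key risk factors, Table 1 makes the blood values conditional, with the words "laboratory parameters (if available". The outcome measure as a whole is given as "Blood pressure, laboratory parameters (if available: low‐density lipoprotein cholesterol, high‐density lipoprotein cholesterol, hemoglobin A_1c_, body weight and body mass index". The bracket opened before the availability condition is never closed, so it is unclear whether the condition stops at HbA1c or also reaches body weight and BMI.

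Section 2.1 lists the same laboratory values with no condition: "laboratory parameters for low density lipoprotein (LDL) cholesterol, high density lipoprotein (HDL) cholesterol", followed by HbA1c. Its paragraph does refer the reader to the table: "Secondary objectives (Table 1) included the assessment".

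Section 2.2 names, as secondary outcomes, percentage changes to the second visit in "key risk factors (including blood pressure and laboratory parameters", again without the condition. It does not name lipids or HbA1c individually. Section 2.3 then gives the percentage changes in key risk factors as an example of a key secondary endpoint, for which post-hoc power calculations are planned.

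On follow-up, section 4.1 states that "there are no clinical follow‐ups outside the standard of care during the 12‐month period" and that "the patients will only follow standard of care".

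**The concern.** A value that exists only because someone in routine care ordered the test is a post-randomisation event. If the analysis uses whoever has values at baseline and at Visit 2, the analysed set is fixed after randomisation and need not have the balance that randomisation gave. The case mix among tested patients, such as the share with diabetes, could then differ between arms and create or hide an app effect on HbA1c or lipids.

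Sections 2.1 to 2.3, read without Table 1, present these outcomes as full randomised comparisons of some standing. The gap also touches patients who complete follow-up and every questionnaire but have no blood value. The comparison proposed in section 4.2, between patients with and without follow-up, does not address them and is not described as being made by arm.

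**Working it through.** **What the text supports.** Setting the sections side by side:

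- Table 1: laboratory values conditional on availability.
- Section 2.1: the same values, no condition, but Table 1 is cited.
- Section 2.2: laboratory parameters, no condition.
- Section 2.3: percentage change in key risk factors treated as key secondary.
- Section 4.1: standard-of-care follow-up only. The article nowhere states that blood tests are required at Visit 2.

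That routine care determines who has a value is an inference from Table 1 and section 4.1 together. No section says it outright.

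**No figure to reproduce.** The document gives no availability rate. Its sample-size figures concern the primary endpoint and do not bear on this point. What follows is illustration.

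**Precision.** Inputs: 332 patients per arm (Table 3), two-sided 5% level, 80% power; availability *a* is assumed equal in both arms. The detectable difference in SD units is (1.960 + 0.842) × √(2 / (332*a*)).

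| Availability | Patients per arm | Detectable difference (SD) |
|---|---|---|
| 100% | 332 | 0.217 |
| 80% | 266 | 0.243 |
| 70% | 232 | 0.260 |
| 50% | 166 | 0.308 |
| 30% | 100 | 0.397 |

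**Bias, general form.** Assume no true effect, and a latent propensity to be tested that correlates ρ with the outcome. The mean outcome among tested patients is shifted by ρ × φ(c)/*a*, where c is the normal quantile at 1 − *a* and φ the normal density. The bias is the difference in this shift between arms.

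| Availability, active vs control | Bias (SD), ρ = 0.2 to 0.4 | Type I error |
|---|---|---|
| 70% vs 70%, same mechanism | 0 | 5.0% |
| 75% vs 65% | 0.03 to 0.06 | 6.1% to 9.6% |
| 80% vs 60% | 0.06 to 0.12 | 9.6% to 24.1% |

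**Bias, HbA1c example.** The only input from the document is the 17.6% with diabetes (Table 3). Assumed: 90% of patients with diabetes tested in both arms; of the others, 30% to 50% tested in control and 60% to 70% in active; HbA1c falls by 0.5 to 1.0 points in patients with diabetes and is unchanged in the others, with no app effect.

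Diabetes share among tested = 0.176 × 0.90 / (0.176 × 0.90 + 0.824 × t), with t the testing rate in the others.

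- Control, t = 0.30: 0.1584 / 0.4056 = 39.1%
- Control, t = 0.50: 0.1584 / 0.5704 = 27.8%
- Active, t = 0.60: 0.1584 / 0.6528 = 24.3%
- Active, t = 0.70: 0.1584 / 0.7352 = 21.5%

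Smallest spurious difference: (0.278 − 0.243) × 0.5 = 0.018 points. Largest: (0.391 − 0.215) × 1.0, which is 0.175 points with unrounded shares. In this example the control arm would show the larger mean fall, so the selection would work against the app.

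Within each diabetes stratum the assumed change is the same in both arms, so adjustment for diabetes removes this difference. That holds because the example lets selection act only through diabetes.

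**The case against.** Several points on the other side stand. Section 2.1 cites Table 1, and section 2.2 speaks only of laboratory parameters in general, so the mismatch is an omission in a condensed text. A reader might infer that the sections contradict each other; they do not, since neither says that values are required from every patient.

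A reader might also infer that the laboratory comparison is biased. The document does not support that. The visit schedule belongs to the full protocol and to the flow chart, neither of which is shown, and lipids and HbA1c may be taken almost universally at Visit 2. Equal availability by the same mechanism gives no bias. The app content described in section 1.4 and the appendix concerns medication, weight, smoking and exercise, and no prompt to have blood tested is mentioned. The HbA1c range follows from assumed testing rates, its lower end is negligible, and no LDL or HDL bias in clinical units was worked out.

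Handling of missing values may well be in the SAP, so its absence here is no finding.

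What remains is narrower. The condition is written in this document and determines who can have the endpoint, and an SAP cannot recover values never measured. A difference between arms is also plausible: patients can tell whether they receive support, the active app displays cardiovascular risk, and the trial itself lists an effect on health-care utilisation as a secondary objective.

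**Conclusion.** The point holds as a minor one. A condition that determines who contributes to the laboratory outcomes appears in Table 1 only, with an unclosed bracket that leaves weight and BMI uncertain, while section 2.3 gives the risk-factor changes the rank of key secondary endpoints.

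On the likely reading that routine care supplies the Visit 2 values, precision is lost whenever availability is incomplete. Bias arises only if availability, or its relation to the outcome, differs between arms. The document neither shows nor excludes this, and the size cannot be derived from it; 0.02 to 0.18 HbA1c points is what the assumed testing rates give, not an estimate for this trial. The primary endpoint and the sample size are unaffected.

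**What to change.** No additional blood draw is needed.

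1. Repeat the availability condition in sections 2.1 and 2.2, and close the bracket in Table 1 so that it is clear whether weight and BMI fall under it.
2. Label the laboratory outcomes exploratory, and take them out of the key secondary endpoints in section 2.3.
3. In place of an unadjusted percentage change, compare Visit 2 values between arms in a model adjusted for the baseline value, diabetes and statin use. The last two are already collected (Table 3).
4. Report by arm the number and baseline characteristics of patients with both values, and state that adjustment removes selection only on the measured covariates.

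A rule that withholds a randomised conclusion when availability differs between arms is not advised: it would need a threshold, and equal rates do not exclude selection.

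The cost is a few wording changes and one adjusted model on data already held. The downside is that the laboratory results carry less weight.
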